#### Psychological impact

The impact of cataracts is greater than the immediate visual impairment and can be associated with psychological co-morbidities such as increased symptoms of anxiety and depression. The third outcome, reductions in depressive, anxiety and somatic symptoms, will be assessed using the self-reporting questionnaire-20 (Vietnamese version) [11]. Each of the 20 questions scores either a zero or one. A score of one indicates that the symptom was present during the past month and a score of 0 indicates that the symptom was absent. The maximum score is 20.

#### Demographic information

Basic demographic information is collected as explanatory variables, including the presence of co-morbidity which is assessed based on self-reported illness episodes [19]. The question asks: How many times in the last 4 weeks have you: (a) stayed in bed or been absent from work for at least one day due to illness; (b) had reduced working capacity (not able to perform usual functions) and (c) used any kind of medical or traditional treatment.

### Statistical considerations

Improvements in the physical functioning domain following cataract surgery have been shown in both an older US and an older Spanish population, 3.2 and 4.0 point improvements respectively [4,20]. The sample size for this study has been calculated on the basis of detecting improvements in this primary outcome measure following cataract surgery. Assuming a lost to follow up rate of 40%, 266 participants would be needed to detect a 4-point difference in the physical functioning domain with 90% power, a 5% two sided significance level, and a standard deviation of 17 [20]. We will oversample in order to allow sufficient numbers to also investigate the secondary outcomes, the household economic and psychological impact of visual impairment, so will recruit a total of 400 individuals who have cataract surgery across the four study sites. The number of participants recruited from each program site will be proportionate to the number of people living in the region and prevalence of visual impairment in the region.

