### Statistical analysis

For descriptive purposes, baseline characteristics will be presented for the surgical group (those who have had cataract surgery) and the non-surgical group (those who have not had surgery). Discrete variables will be summarised by frequencies and percentages. Continuous variables will be summarised by use of standard measures of central tendency and dispersion, including median and inter-quartile ranges given potential skewness in the data.

We will calculate mean changes in the SF-12v2 scores for the surgical and non-surgical participants at the six months and one year follow up points. Reductions in scores indicate deterioration and improvements in scores indicate an improvement in quality of life. Generalised linear models will be used to assess multivariate-adjusted mean differences in SF-12v2 scores comparing surgical and non-surgical participants.

To assess the impact of cataract surgery on household economic circumstances and psychological outcomes, models will be constructed based on each of the secondary and tertiary outcomes listed above. For the dichotomous outcomes, 'returned to work', change in household income and economic hardship, the models will be estimated through logistic regression. Household wealth and psychological impact, specified as continuous outcomes, will be modelled using parametric or non-parametric methods depending on the distributional characteristics of each outcome. The modelling will account for the potential random effects, as each individual respondent will yield multiple measures.

The cost-effectiveness analysis will take a societal perspective. The costs of surgery will be assessed through financial statements provided by Vietnam Blindness Prevention Program staff. These will include staff, travel and training costs associated with running the cataract surgery program, including the costs of the operations. Cost-offsets in terms of use of health care services and medications will be assessed based on individual self-report in the follow up interviews. Effectiveness will be assessed in terms of quality of life, using the SF-12v2, with incremental cost-effectiveness ratio estimated based on cost per quality adjusted life years.

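### The stated 90% power belongs to a single-group before-after change, not to the planned surgical versus non-surgical comparison of SF-12v2, for which no group size is given

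*Protocol article*

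**What the plan says.** Under Statistical considerations, the article cites improvements of 3.2 and 4.0 points in two earlier studies: "Improvements in the physical functioning domain following cataract surgery have been shown in both an older US and an older Spanish population". It then states: "The sample size for this study has been calculated on the basis of detecting improvements in this primary outcome measure following cataract surgery". The resulting figure is "266 participants would be needed to detect a 4-point difference in the physical functioning domain with 90% power", with "a 5% two sided significance level, and a standard deviation of 17", allowing for 40% loss to follow-up. To leave room for the secondary outcomes the target is raised: "so will recruit a total of 400 individuals who have cataract surgery across the four study sites".

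Under Statistical analysis, mean changes in SF-12v2 are to be calculated separately for surgical and non-surgical participants at six months and one year. The only model named for this outcome is comparative: "Generalised linear models will be used to assess multivariate-adjusted mean differences in SF-12v2 scores comparing surgical and non-surgical participants".

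The section on the 6 and 12 month interviews says that people who do not have surgery are also followed up. The text of the article gives no target, minimum, expected number or ratio for that group.

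**The concern.** The sample size answers whether physical functioning changes after surgery in those operated on. The named model answers whether operated and non-operated people differ. These are different contrasts with different variances. In the second, precision depends heavily on the smaller group, and here the non-surgical group is simply whoever is referred and does not have the operation.

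The Overview gives the impact of cataract surgery as the primary aim, so the comparison is a result that readers will look to. If they carry the 90% over to it, a non-significant difference could be taken as evidence of no benefit from an adequately powered study. The Abstract says the study is meant to inform investment in eye-health services, so that misreading would matter.

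**Working it through.** **Inputs from Statistical considerations.** Difference 4 points; SD 17; two-sided 5% (z = 1.960); power 90% (z = 1.2816, sum 3.2415); loss 40%; 400 surgical participants.

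**Step 1: reproduce 266.**
- Single group: n = (17 × 3.2415 / 4)² = 189.8, so 190. Then 190 × 1.4 = 266, an exact match.
- Two groups: n = 2 × 189.8 = 380 per group, or 760 in total before any loss. One-sided testing or 80% power brings this down only to between 448 and 620 in total before loss. None of these gives 266.

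**Step 2: check the single-group figure, taking 17 as the SD of the change.** Multiplying by 1.4 does not offset a 40% loss; dividing by 0.6 does.
- 190 / 0.6 = 317 recruited are needed for 90% power.
- 266 × 0.6 = 159.6 evaluable: power = Φ(4/17 × √159.6 − 1.96) = Φ(1.01) ≈ 84%.
- 400 × 0.6 = 240 evaluable: power = Φ(4/17 × √240 − 1.96) = Φ(1.69) ≈ 95%.

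**Step 3: power of the planned comparison.** With n surgical and m non-surgical completers and a common SD, power = Φ(4 / (SD × √(1/n + 1/m)) − 1.96). The CI half-width is 1.96 × SD × √(1/n + 1/m). The values of m are assumed, because the text gives none.

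With n = 240:

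| m | Power, SD 17 | 95% CI half-width, SD 17 | Power, r = 0.5 to 0.6 |
|---|---|---|---|
| 30 | 23% | 6.5 | 29–33% |
| 60 | 37% | 4.8 | 47–53% |
| 100 | 51% | 4.0 | 63–70% |
| 240 | 73% | 3.0 | 85–90% |

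The last column supposes that 17 is the SD of a single score and that the model adjusts for baseline, with an assumed baseline to follow-up correlation r. The residual SD is then 17 × √(1 − r²), which is 14.7 at r = 0.5 and 13.6 at r = 0.6.

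**Step 4: no loss at all, SD 17.** With 400 surgical participants and 50, 100, 200 or 400 non-surgical, power is about 35%, 56%, 78% and 91%.

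**The case against.** The strongest reply is that the article never claims 90% power for the comparison. It ties the calculation to improvement after surgery, takes its effect size from such improvements, and also plans mean changes for the surgical group. That is fair. A reader might infer that the authors asserted adequate power for surgical versus non-surgical, but the wording does not go that far. What stands is that the calculation describes one contrast, the only inferential model for SF-12v2 addresses another, and the second has no statement of power or precision.

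A second reply is that one SD and one loss rate overstate the problem. This holds in part. The article does not say whether "a standard deviation of 17" refers to a change or a single score, and under favourable assumptions a large non-surgical group comes close to or reaches 90%. Surgery is not randomised, however, so covariates related to surgery status could also widen the standard error. At 30 or 60 non-surgical completers, power stays at 33% or below and 53% or below in the scenarios with 40% loss.

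Third, the increase to 400 might seem to settle the matter. It adds surgical participants only, and the article justifies it by the secondary outcomes.

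Finally, Figure 1 was not available for checking and the article condenses a fuller protocol, so a non-surgical number may exist elsewhere. The statement that none is given is limited to the article's text.

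**Conclusion.** The point holds as a mismatch between the powered contrast and the analysed one. The 266 is a single-group figure, and the 90% attached to it cannot be carried to the surgical versus non-surgical difference. It is not exact for the single-group change either: about 84% at 266 recruited, although about 95% at the target of 400.

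For the comparison, power for 4 points runs from about 23% to about 91% over the scenarios examined, driven mainly by a number that the text does not give. These figures rest on an equal SD in both groups, assumed non-surgical numbers, an assumed r where adjustment is considered, and either 40% loss or none.

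Two stronger readings are not supported. One is that the comparison is certain to be badly underpowered: with a large non-surgical group and low loss or useful baseline adjustment it need not be. The other is that the study is too small for its stated calculation: at 400 surgical participants the before-after change is well covered if 17 is the SD of that change.

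**What to change.** 1. State that the power calculation covers only the change within the surgical group, and name that change as the powered analysis.
2. Correct its figure: with 40% loss, 266 recruited gives about 84% power, 317 would be needed for 90%, and the target of 400 gives about 95%.
3. Say whether the SD of 17 is for a change or for a single score, and redo item 2 if it is the latter.
4. For the surgical versus non-surgical difference, add a short table of power or expected CI half-width over a range of non-surgical completers, SD and loss.
5. Report that difference as an estimate with its CI, and state that a non-significant result will not be read as no effect.

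The cost is rewording and one small table. No extra participants are needed. The only downside is a less favourable stated power for the comparison.

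### The stated requirement of 266 multiplies 190 by 1.4 rather than dividing by 0.60; on the reading that reproduces it, 40% loss requires 317, which the planned 400 still covers

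*Protocol article*

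**What the plan says.** The Statistical considerations section of the protocol article says that the sample size was "calculated on the basis of detecting improvements in this primary outcome measure following cataract surgery". It then gives the requirement: "Assuming a lost to follow up rate of 40%, 266 participants would be needed to detect a 4-point difference in the physical functioning domain". The remaining inputs are 90% power, "a 5% two sided significance level, and a standard deviation of 17". The section also cites earlier improvements of 3.2 and 4.0 points in two older populations.

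The 266 is not the recruitment target. The section goes on to say that the study will oversample to support the secondary economic and psychological outcomes, "so will recruit a total of 400 individuals who have cataract surgery across the four study sites".

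The text does not name the test behind the 266, and it does not say whether 17 is the SD of a score or of a change.

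**The concern.** If 40% of recruits are lost, 60% remain, so the number to recruit is the evaluable number divided by 0.60. Multiplying by 1.4 gives too few: 60% of 1.4 times the requirement is only 84% of it. At small loss rates the two rules nearly agree, but at 40% they differ materially. The 266 is exactly what the multiplication gives from the section's own inputs.

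Two things are affected. The power claimed for 266 does not hold under the loss the plan itself assumes. The move to 400 is also presented as an oversample above the primary requirement, so an understated requirement makes that oversample look larger than it is.

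**Working it through.** **Inputs** (all from Statistical considerations): difference 4 points; SD 17; 90% power (z = 1.28155); two-sided 5% (z = 1.95996); loss to follow-up 40%; 400 surgical recruits planned.

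**Assumed test.** Single-group pre-post comparison, with 17 as the SD of the within-person change. The stated aim of detecting improvement after surgery and the absence of an allocation ratio point this way, but the text does not say so.

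**Reproducing the plan's figure**

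- Evaluable n = (1.95996 + 1.28155)² × 17² / 4² = 189.8, rounded up to 190.
- 190 × 1.40 = 266.0, the stated figure exactly.

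**Correct allowance for loss**

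- 190 / (1 − 0.40) = 316.7, so 317.
- With the t distribution, 192 evaluable are needed: 192 / 0.60 = 320.
- Shortfall in the stated figure: 317 − 266 = 51, or 51/317 = 16% of the corrected requirement.

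**Other readings, dividing by 0.60**

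| Reading | Evaluable | Recruits |
|---|---|---|
| Pre-post, one-sided 5%, 90% power | 154.7 | 258 |
| Pre-post, two-sided 5%, 80% power | 141.8 | 237 |
| Pre-post, two-sided 5%, 90% power, t | 192 | 320 |
| Two equal groups, SD 17, 90% power | 760 in total | above 1,200 |

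None gives 266. For 266 to be correctly inflated, 159.6 evaluable would have to suffice. That needs a change SD of 4 × √159.6 / 3.2415 = 15.6. If 17 were the SD of a single score, a change SD of 15.6 means 17 × √(2(1 − ρ)) = 15.6, so ρ is about 0.58. The section states no correlation.

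**Power on the pre-post reading, with 40% loss**

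Power = Φ(δ√n / 17 − 1.96).

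| Recruited | Evaluable | δ | Power (normal) | Power (t) |
|---|---|---|---|---|
| 266 | 159.6 | 4.0 | 84.4% | 84.0% |
| 317 | 190.2 | 4.0 | 90.1% | 89.8% |
| 400 | 240 | 4.0 | 95.4% | 95.3% |
| 400 | 240 | 3.2 | 83.0% | not computed |

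**Loss that each number tolerates at 90% power** (normal approximation)

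- 266: 1 − 190/266 = 28.6%.
- 400: 1 − 190/400 = 52.5%.

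**Oversampling margin at 400**

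- Against 266: 400 − 266 = 134; 134/266 = 50%.
- Against 317: 400 − 317 = 83; 83/317 = 26%.

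**The case against.** The strongest reply is that nobody plans to recruit 266. The target is 400 people who have surgery, which exceeds 317 and gives about 95% power for 4 points after the assumed loss. The error changes no target, endpoint or analysis. This stands, and it limits the point to a misstated intermediate figure and the margin measured from it.

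A reader might infer that 266 is a minimum on which the study could fall back if recruitment were slow, so that the error threatens the primary result. The article does not support that. It nowhere makes 266 a floor, a stopping point or an acceptable shortfall, so the 84% describes a study that is not planned.

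A reader might also infer that the smaller margin leaves the secondary outcomes short. The article gives no calculation or required margin for them, so nothing shows that 83 extra recruits are too few.

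Finally, the pre-post test and the meaning of the SD are inferred, and the SD comes from a cited source that is not at hand. That is a fair caution, and every power figure here depends on it. It does not rescue the 266: the stated inputs give it exactly through multiplication by 1.4, whereas correct inflation reaches it only by adding an assumption that the text does not contain.

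**Conclusion.** The stated requirement is wrong on its own inputs. On the reading that reproduces it, 266 should be 317 (about 320 by t), and 266 recruits with 40% loss would give about 84% power rather than 90%. The size of the problem is 51 recruits in the stated requirement and an oversampling margin of 26% where the text implies 50%. It is a correction to the text and not a threat to the study.

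It would be too strong to say that the pre-post test is underpowered: 400 recruits leave about 240 evaluable, with about 95% power for 4 points and 83% for 3.2 points. It would be equally wrong to take the 95% as reassurance about the comparison of surgical with non-surgical participants in the Statistical analysis section. That is a different contrast, the article gives no number for the non-surgical group, and this calculation says nothing about its power.

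The conclusion rests on a single-group pre-post test, 17 as the SD of the change, and 40% loss among surgical recruits.

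**What to change.** In Statistical considerations:

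- Replace 266 with 317, or with about 320 if the t distribution is used, and show the step as 190/0.60 (or 192/0.60).
- Name the assumed test as a single-group pre-post comparison and state that 17 is the SD of the within-person change. If either assumption is not what was meant, give the intended inputs and recompute.
- State that 400 surgical recruits leave about 240 evaluable at 40% loss, with about 95% power for 4 points and 83% for 3.2 points in that pre-post calculation. Make no claim there about the surgical versus non-surgical comparison.

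The cost is two or three sentences. This point alone gives no reason to change the target of 400.

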### Statistical analysis

For descriptive purposes, baseline characteristics will be presented for the surgical group (those who have had cataract surgery) and the non-surgical group (those who have not had surgery). Discrete variables will be summarised by frequencies and percentages. Continuous variables will be summarised by use of standard measures of central tendency and dispersion, including median and inter-quartile ranges given potential skewness in the data.

We will calculate mean changes in the SF-12v2 scores for the surgical and non-surgical participants at the six months and one year follow up points. Reductions in scores indicate deterioration and improvements in scores indicate an improvement in quality of life. Generalised linear models will be used to assess multivariate-adjusted mean differences in SF-12v2 scores comparing surgical and non-surgical participants.

To assess the impact of cataract surgery on household economic circumstances and psychological outcomes, models will be constructed based on each of the secondary and tertiary outcomes listed above. For the dichotomous outcomes, 'returned to work', change in household income and economic hardship, the models will be estimated through logistic regression. Household wealth and psychological impact, specified as continuous outcomes, will be modelled using parametric or non-parametric methods depending on the distributional characteristics of each outcome. The modelling will account for the potential random effects, as each individual respondent will yield multiple measures.

The cost-effectiveness analysis will take a societal perspective. The costs of surgery will be assessed through financial statements provided by Vietnam Blindness Prevention Program staff. These will include staff, travel and training costs associated with running the cataract surgery program, including the costs of the operations. Cost-offsets in terms of use of health care services and medications will be assessed based on individual self-report in the follow up interviews. Effectiveness will be assessed in terms of quality of life, using the SF-12v2, with incremental cost-effectiveness ratio estimated based on cost per quality adjusted life years.

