***Employment***			

Main lifetime occupation	✓		

Time spent doing paid work	✓	✓	✓

Time spent doing unpaid work	✓	✓	✓

Impact of eyesight on ability to work	✓	✓	✓

Return to work (paid/unpaid)		✓	✓

Income support	✓	✓	✓

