***Household economic situation***			

Annual income	✓	✓	✓

Main source of income	✓	✓	✓

Estimated value of assets (non-livestock and live-stock)	✓	✓	✓

Asset ownership	✓	✓	✓

Financial assistance	✓	✓	✓

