#### Economic circumstances and health care utilisation

The secondary outcomes, which cover household economic circumstances and health care utilisation, are assessed via the following indicators: employment status; household income; household wealth; household economic hardship and health care utilisation.

To assess *employment status*, questions on time spent in paid and unpaid work for the participant are modified from questions 6-8, 12b and 26-27 from Section 4b of the 2006 Vietnamese Household Living Standards Survey [13]. The average number of hours of paid and unpaid work performed per week over the previous 12 months will be calculated. In addition, at six and 12 months participants are asked to indicate whether, and in what capacity, they have returned to work (paid and unpaid): same job, similar job, different job and the average number of hours worked per week. The date of return to partial or full-time work will be recorded.

The main source of *household income *is modified from questions 12(a-e) in Section 4b of the 2006 Vietnamese Household Living Standards Survey [13]. Participants are also asked about annual income and whether they are receiving any income support payments (sickness, disability, or unemployment payments provided by the Government) or health-insurance benefits.

*Household wealth *is measured using questions that cover key aspects of socioeconomic well-being including details of the dwelling construction and ownership and value of a small number of assets and will be combined into an index of household wealth [14].

*Household economic hardship *will be determined by a series of questions about failure to pay basic living and medical expenses and whether there was help provided by any organisation or individual to meet these payments. An advantage of this measure is that it is sensitive to the possibility that individuals prioritise certain payments (e.g. forgo medical expenses to pay school fees). The basis for these questions comes from the US Census Survey of Income and Program Participation [15] and a modified version has been used in the authors' previous work [16-18]. Economic hardship will be constructed as a dichotomous variable where a reported inability to make any one of the payments posed to respondents will be classed as a case of economic hardship.

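### Household income is collected as an annual amount at every visit, but its change is analysed as a yes/no outcome with no stated cut-point, which discards information that a continuous analysis would keep

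*Protocol article*

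**What the plan says.** All references are to the protocol article.

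- **Collection.** Table 1, under Household economic situation, has the row "Annual income" ticked at baseline, 6 months and 12 months. The section on economic circumstances and health care utilisation adds: "Participants are also asked about annual income and whether they are receiving any income support payments". The same part of the article divides out-of-pocket spending by annual household income, so income is meant to be available as a number.
- **Analysis of income.** Statistical analysis names return to work as the first of the dichotomous outcomes and continues: "change in household income and economic hardship, the models will be estimated through logistic regression". No threshold, direction or reference period for a change in income is given.
- **Analysis of wealth.** The next sentence reads: "Household wealth and psychological impact, specified as continuous outcomes, will be modelled using parametric or non-parametric methods", the choice depending on the distribution of each outcome.
- **Hardship, for contrast.** Here the dichotomy has a rule: "Economic hardship will be constructed as a dichotomous variable where a reported inability to make any one of the payments" is enough to count as a case.
- **Sample size.** Statistical considerations sizes the study on the physical functioning domain of the SF-12v2 only. It then raises recruitment to 400 surgical participants so that the secondary outcomes can also be studied. It gives no number for the non-surgical group.

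**The concern.** Hardship is naturally binary, because it is built from failures to make payments. Income is not: it is an amount, asked three times. Collapsing its change to yes/no removes the size of the change, so a household that gains a little counts the same as one whose income doubles. It also makes the result depend on a cut-point that the article does not give.

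Two things are at stake. The first is power on an outcome for which the recruitment target was deliberately raised. The second is interpretability. The Discussion names the value of lost income as an indicator of the cost of visual impairment, and an odds ratio for whether income changed cannot supply a value.

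**Working it through.** **The plan's own figure.** No power or sample size is stated for income. The one stated figure, 266, belongs to the primary outcome. It reproduces as n = (17 × (1.960 + 1.282) / 4)² = 189.8, so 190, and 190 × 1.40 = 266. It has no bearing on income and is shown only to make clear that no planned income figure exists to check against.

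**Information kept by a split.** Assume that income change is normal on some scale, with a shift between groups. The efficiency of a yes/no split, relative to the continuous comparison and for a small shift, is φ(c)² / [p(1 − p)]. Here c is the cut-point in SD units, φ the standard normal density, and p the proportion above the cut.

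| Split | φ(c) | p(1 − p) | Efficiency |
|---|---|---|---|
| 50/50 | 0.399 | 0.25 | 0.637 (= 2/π) |
| 70/30 | 0.348 | 0.21 | 0.576 |
| 80/20 | 0.280 | 0.16 | 0.490 |
| 90/10 | 0.175 | 0.09 | 0.342 |

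The median split is the best case.

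**What that means for power.** Inputs:
- 240 surgical completers = 400 × (1 − 0.40). This applies the protocol's 40% loss rate, which it states for the primary outcome calculation, to its target of 400.
- 60, 120 or 240 non-surgical completers (assumed range; the article gives no number).
- A difference of 0.3 SD (assumed), two-sided 5% level.

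Continuous: power = Φ[0.3 / √(1/240 + 1/n₂) − 1.960].

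Split: the proportion above the cut is p₀ in the non-surgical group and p₁ = 1 − Φ(c − 0.3) in the surgical group. Power = Φ[(p₁ − p₀ − 1.960 × SE₀) / SE₁], with SE₀ pooled and SE₁ unpooled.

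Worked for n₂ = 120:
- Continuous: √(1/240 + 1/120) = 0.1118; 0.3 / 0.1118 − 1.960 = 0.723; power 77%.
- Median split: p₀ = 0.500, p₁ = 0.618, SE₀ = 0.0552, SE₁ = 0.0554; power 57%.
- 80/20 split: p₀ = 0.200, p₁ = 0.294, SE₀ = 0.0492, SE₁ = 0.0469; power 48%.

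| Non-surgical completers | Continuous | Median split | 80/20 split |
|---|---|---|---|
| 60 | 55% | 39% | 29% |
| 120 | 77% | 57% | 48% |
| 240 | 91% | 74% | 67% |

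From unrounded values, the loss is about 16 to 20 percentage points at the median and 24 to 29 at 80/20.

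**The case against.** **The source of the binary variable is not spelled out.** The article does not say that the yes/no change is derived from the annual amount. Table 1 also has an item on the impact of illness on household income, and the dichotomy might come from that. This stands as an uncertainty. It does not remove the point: the amount is collected at every visit, and the only method named for income change is a logistic model.

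**Self-reported income is noisy and skewed.** Many participants will come from farming provinces, and the plan itself anticipates skewness, so a yes/no change is a defensible, if less efficient, choice for a secondary outcome. Part of this stands: on the raw scale a comparison of means would itself be inefficient, and the gains above assume a suitable transformation or rank-based method. But the plan already allows exactly that flexibility for wealth, so skewness alone does not explain why income is treated differently.

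**The size is illustrative.** The 64% needs normality and a median cut, and 240 counts surgical completers only. Both limits are accepted.

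**A stronger reading on work.** The article says that "participants are asked to indicate whether, and in what capacity, they have returned to work (paid and unpaid"), and 'returned to work' is also in the logistic list. A reader might infer that this model includes people who never stopped working, or that hours worked are left out. The documents do not support either. No denominator or coding is stated, and the question itself presupposes an earlier stop. Skip rules and the population at risk may sit in the full interview schedule or analysis plan, which are not shown. The plan also promises a model for every secondary outcome, so hours are not excluded. This is not raised as an error.

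**Conclusion.** The point holds for income. The plan fixes a dichotomous analysis of an outcome collected as an amount, gives no cut-point, and treats it differently from wealth without a reason. Under an assumed normal change on some scale, at most about 64% of the information is kept, falling to 49% at an 80/20 cut. The power losses tabulated above rest further on the assumed 0.3 SD difference and the assumed non-surgical numbers, so they indicate scale and are not a forecast. The loss of the size of the change does not depend on those assumptions. The outcome is secondary, and the SF-12v2 analysis and its sample size are untouched. The change is worth making but is not critical to the study's main conclusion.

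**What to change.** In Statistical analysis, move change in household income out of the list of dichotomous outcomes and specify:

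1. **Main income analysis:** annual household income as a continuous outcome, log-transformed or analysed by a rank-based or robust method as the plan already allows for wealth. Compare surgical with non-surgical participants, adjust for baseline income, and use the random-effects structure already planned for repeated measures.
2. **Main contrast at 12 months:** follow-up runs from the scheduled surgery date. If annual income refers to the preceding 12 months, the six-month answer still covers about six months before surgery and would dilute any effect. Report six months as secondary.
3. **Supportive analysis:** keep the yes/no version, with its cut-point and source item stated in advance.
4. **Hardship:** keep logistic regression as planned.

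The cost is analysis wording only, since annual income is already collected at all three visits. The small downside is that zero and very skewed incomes need a pre-stated rule, such as a rank-based method or an offset before taking logs.
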